## Abstract

**Background:**

Rehabilitation of patients with chronic obstructive pulmonary disease (COPD) is a key treatment in COPD. However, despite the existing evidence and a strong recommendation from lung associations worldwide, 50% of patients with COPD decline to participate in COPD rehabilitation program and 30–50% drop-out before completion. The main reasons are severe symptoms, inflexible accessibility and necessity for transportation. Currently there are no well-established and evident rehabilitation alternatives. Supervised online screen rehabilitation could be a useful approach to increase accessibility and compliance. The aim of this multicenter RCT study is to compare the potential benefits of a 10-week online COPD rehabilitation program (CORe) with conventional outpatient COPD rehabilitation (CCRe).

**Methods:**

This study is a randomized assessor- and statistician blinded superiority multicenter trial with two parallel groups, employing 1:1 allocation to the intervention and the comparison group.On the basis of a sample size calculation, 134 patients with severe or very severe COPD and eligible to conventional hospital based outpatient COPD rehabilitation will be included and randomized from eight different hospitals. The CORe intervention group receives group supervised resistance- and endurance training and patient education, 60 min, three times/week for 10 weeks at home via online-screen. The CCRe comparison group receives group based supervised resistance- and endurance training and patient education, 90 min, two times/week for 10 weeks (two hospitals) or 12 weeks (six hospitals) in groups at the local hospital. The primary outcome is change in the 6-min walking distance after 10/12 weeks; the secondary outcomes are changes in 30 s sit-to-stand chair test, physical activity level, symptoms, anxiety and depression symptoms, disease specific and generic quality of life. Primary endpoint is 10/12 weeks from baseline, while secondary endpoints are 22, 36, 62 weeks from baseline assessments.

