
Thus, the new results are promising, additional effects from face-to-face supervised COPD tele-rehabilitation in groups compared to outpatient supervised COPD rehabilitation in groups’ remains unanswered, i.e. potential higher compliance and effects when supervised and potentially better resource utilization when delivered in groups. To our knowledge this study protocol currently describes the first RCT study planned to investigate effects from equally face-to-face supervised and group based COPD rehabilitation in outpatient and tele-rehabilitation setting [22].

The purpose of our RCT study is to investigate the potential benefits of a 10-week supervised online COPD rehabilitation program (CORe) with conventional supervised COPD rehabilitation (CCRe) on walking distance (primary outcome), muscle endurance, physical activity level, quality of life, and COPD symptoms after completion of the intervention and at follow-up 3, 6 and 12 month later in patients with severe and very severe (stage III-IV) COPD. This paper describes the rationale and design of the study.

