### Study design

This study is a randomized controlled, assessor- and statistician blinded, superiority, multicentre trial with two parallel-groups. The trial investigates the effect of supervised COPD Online rehabilitation in groups, delivered by health professionals in the patients’ own home via a computer, in patients with severe and very severe (stage III-IV) COPD (ClinicalTrial.gov-identifier: NCT02667171). Patients from the University hospitals in the Capital Region of Denmark will be randomized to the supervised group-based online COPD rehabilitation (CORe) or to the conventional supervised COPD rehabilitation program (CCRe). The primary outcome will be the 6-min walking distance after completion of the COPD rehabilitation program (primary end point at 10/12 weeks). In addition, the study collects follow-up data at 3, 6 and 12 months after completion of the program which will be published in a separate paper (Fig. 1 and Table 1).

**Table 1 Tab1:** Study measures and outcomes to be collected

Variable	Baseline	10/12 weeks (post)	3-month follow-up (22-weeks)	6-month follow-up (36-weeks)	12-month follow-up (62-weeks)
Primary outcomes					
6 min walk distance (6MWD)	X	X	X		X
Secondary outcomes					
30s sit-to-stand test (30STS)	X	X	X		X
Clinical COPD Questionnaire (CCQ)	X	X	X		X
COPD Assessment Test (CAT)	X	X	X		X
Hospital Anxiety Depression Scale	X	X	X		X
EuroQol 5D (3-L)	X	X	X		X
Other variables and outcomes					
Attendance in rehabilitation		X			
Number of COPD related hospital admissions	X	X	X	X	X
Number of COPD hospital days	X	X	X	X	X
COPD related outpatient visits	X	X	X	X	X
Number of COPD exacerbations	X	X	X	X	X
Mortality	X	X	X	X	X
Exploratory outcome					
24 h–mobility (ActivePAL3tm; 5 days)	X	X	X		X
Descriptive variables					
Lung function	X				X
FVC	X				X
FEV1	X				X
FEV1/FVC%	X				X
FEV1% expected	X				X
Charlson morbity Index	X				X
Anthropometric measures					
Gender	X				
Age	X				
Weight	X	X	X		X
Height	X	X	X		X
Body Mass Index (BMI)	X	X	X		X
Self-reported measures					
Smoking status	X	X	X		X
Pharmacologic treatment	X	X	X		X

The primary hypothesis is that CORe is superior to CCRe due to a higher compliance and adherence to the CORe program. We expect a mean between-group difference of 26 m in the 6-min walk test after completion of the COPD rehabilitation programs (primary endpoint at 12-weeks).

We also expect clinically relevant improvements in both groups as a results of completing the COPD rehabilitation (Table 1).

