#### Comparison group - conventional COPD rehabilitation programme (CCRe)

Patients in the comparison group will receive the supervised standard COPD Rehabilitation program (CCRe) for patients with severe and very severe (stage III-IV) COPD, which follows the Danish Health Authority’s National Clinical Guideline and the Regional Guidelines [6, 29, 30]. The guidelines allow for minor variations in the duration of the program (from 10 to12 weeks) but not in the content of the program [6, 29, 30]. The rehabilitation program contains exercise and patient education. Exercise sessions last 60 min twice weekly and will be supervised by skilled physiotherapists with at least 2 years of experience with COPD rehabilitation. The content of the physical exercises is presented in Table 4. Patient education sessions of 60–90 min will take place once weekly following the exercise session. The total number of patient education sessions will vary from 10 to 12 lessons (including follow-up sessions). Topics covered in the education program are presented in Table 5.

**Table 4 Tab4:** Exercise content comparison group - conventional COPD rehabilitation

Exercise type	Exercises	Intensity	Progression
Warm-up (duration 5-10 min)	Sitting or standing: -Heel uprisings (uni- or bilateral), - Kneeextension - rear deltoid row - chest press movement - Vertical shoulder press’ (uni- or bilateral). Standing: -Walking various - leg curl - leg swing - squats	Non-specific intensity Purpose: -increase body temperature - cardiorespiratory warm-up -muscle and tendon tissue Warm-up	none
Endurance training (duration 20-30 min)	-Walking or -Cycle or - Treadmill or - Circuit training or - Activity games	Borg CR-10 dyspnea 4–7 Exercises performed in intervals or continuous	Every 2nd to 4th week load adjustment individualized
Resistance training Duration 20-30 min)	Machine: -leg press -knee extension Pull down and/or chestpres (vertical) Other equipment for strength circuit training elastic band Dumbbells Weight cuff	40–80% of 1RM corresponding from 8 to 25 repetitions 2-3sets	Every 2nd to 4th week load adjustment individualized (repetition counting by supervisor)
Cool-down (duration5-10 min)	Breathing exercises Pursed lip breathe Relaxation exercises Yoga exercises	Non-specific intensity	Non-specific

Responsible health profession: Physiotherapist

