### Reliability calculations

Intra- and inter tester reliability will be calculated on physical outcome measures (6MWT and 30s-STS) in fifty consecutively recruited patients. The retest is completed seven to 10 days after baseline assessment and prior to intervention start. The reliability in the patient reported questionnaires (CAT, CCQ, HADS, EQ-5D) will be calculated in the same sample of fifty patients.

The reliability for the physical outcome measures and patient reported outcomes will be published in separate articles.

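### Visit timing has two anchors that agree only for a 10-week programme, so in six of eight hospitals either exposure time or time since completion differs by arm

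*Protocol article*

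**What the plan says.** **Programme length.** The abstract gives CORe as "three times/week for 10 weeks at home via online-screen" and CCRe as "two times/week for 10 weeks (two hospitals) or 12 weeks (six hospitals) in groups at the local hospital". Under Randomization, allocation is 1:1 within each recruiting hospital.

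**Post visit and primary endpoint.** The Study design section first places the primary 6MWD assessment after the programme ends, at 10/12 weeks. Later in the same section, where the hypothesis is stated, it gives the primary endpoint as 12 weeks.

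**Follow-up visits.** The abstract counts from baseline: "Primary endpoint is 10/12 weeks from baseline, while secondary endpoints are 22, 36, 62 weeks from baseline assessments". The Study design section counts from the end of the programme: "the study collects follow-up data at 3, 6 and 12 months after completion of the program". The accelerometer paragraph under Secondary outcome measures also counts from completion. Table 1 treats the two as the same, labelling the 3-month visit as week 22, the 6-month visit as week 36 and the 12-month visit as week 62.

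**Events.** Table 1 lists "Number of COPD related hospital admissions", together with hospital days, outpatient visits, exacerbations and mortality, at the 10/12-week visit and at every later visit. The section on other variables and outcomes says that they come from the hospital registry and serve as descriptive and explanatory variables.

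**Purpose.** The Background promises walking distance, quality of life and symptoms, among others, "after completion of the intervention and at follow-up 3, 6 and 12 month later". Table 1 marks none of these at 36 weeks.

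**The concern.** Sites cannot meet both definitions for a CCRe patient on a 12-week programme. Because randomization is within hospital, any timing rule tied to completion makes timing differ by arm inside those six hospitals. The random hospital effect in the analysis model cannot remove a difference between arms within a hospital.

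Three things are at stake:

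- **The primary comparison.** A CORe patient at a 12-week hospital may be tested at week 10 (straight after finishing, two weeks before the CCRe patients there) or at week 12 (with them, but two weeks after finishing). These are different comparisons, and the text does not choose between them.
- **The event counts.** If counts are cut at a completion-based visit, CCRe is observed for longer. With equal event rates that would make CORe look better. These counts are also meant to be explanatory variables for the primary and secondary outcomes, so unequal windows could carry over into those analyses.
- **The objective.** The stated purpose promises six-month results on outcomes that will not be measured then.

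**Working it through.** **Inputs.** CORe 10 weeks; CCRe 10 weeks in two hospitals and 12 in six (abstract). Follow-ups at weeks 22, 36 and 62 from baseline (abstract), or three, six and twelve months after completion (Study design). Months are taken as 12, 26 and 52 weeks.

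**Step 1. Reproduce the stated weeks.** Visit week = programme length + 12, 26 or 52.

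- 10-week programme: 10 + 12 = 22; 10 + 26 = 36; 10 + 52 = 62. These are the abstract's figures.
- 12-week programme: 12 + 12 = 24; 12 + 26 = 38; 12 + 52 = 64. These differ from the abstract by two weeks each.

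In calendar months (365.25 / 12 / 7 = 4.35 weeks), three months after a 10-week programme is week 23.0, so week 22 is itself rounded. The two-week gap between programme lengths remains (week 25.0 for 12 weeks).

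**Step 2. Completion anchor: cumulative counting time.** In a 12-week hospital the ratio is the CCRe week divided by the CORe week. For the arm average, assume equal recruitment per hospital, so that 6/8 of CCRe patients are in 12-week hospitals: mean CCRe week = (2 × 10-week value + 6 × 12-week value) / 8.

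| Visit | CORe week | CCRe week, 12-week hospitals | Excess there | Mean CCRe week | Excess across arm |
|---|---|---|---|---|---|
| Post | 10 | 12 | 12/10: 20.0% | 11.5 | 15.0% |
| 3 months | 22 | 24 | 24/22: 9.1% | 23.5 | 6.8% |
| 6 months | 36 | 38 | 38/36: 5.6% | 37.5 | 4.2% |
| 12 months | 62 | 64 | 64/62: 3.2% | 63.5 | 2.4% |

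**Step 3. Baseline anchor at weeks 22, 36 and 62.** Cumulative counting time is equal in the two arms. Time since completion is not:

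- CORe: 22 − 10 = 12; 36 − 10 = 26; 62 − 10 = 52 weeks.
- CCRe in 12-week hospitals: 22 − 12 = 10; 36 − 12 = 24; 62 − 12 = 50 weeks.

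If the post visit still follows completion, the interval from post visit to week 22 is 12 weeks in CORe and 10 in those CCRe patients, so counts per interval would lean the other way.

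**Step 4. Primary endpoint.** If CORe patients at 12-week hospitals are tested at week 10, timing from baseline differs by arm. If they are tested at week 12, timing is equal but they are two weeks past their last session while CCRe patients have just finished. The document gives nothing from which to turn two weeks into metres, so the effect on 6MWD cannot be sized. The planned sample size is not affected.

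**Step 5. Purpose against schedule.** At 36 weeks Table 1 marks only admissions, hospital days, outpatient visits, exacerbations and mortality. The section on changes to the initial plan agrees: six-month follow-up was planned from register data, and testing was later added at 12 months only. The Background sentence is the one out of line.

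**The case against.** The strongest reply is that no section defines the counting windows, so a bias in event counts is inferred. It needs counts cut at the visit and a visit that follows completion, and the 12-week statement of the primary endpoint leaves open that everyone is tested at week 12. This stands, and the 20% and 15% figures are conditional for that reason. A reader might infer that events are counted longer in CCRe throughout. The documents do not support that: under the abstract's baseline anchor, cumulative windows at weeks 22, 36 and 62 are equal. For those visits, longer counting and unequal time since completion are alternatives, not joint faults.

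It is also fair that these events are neither primary nor secondary outcomes, that registry data can be cut at any date, and that a full protocol or SAP may set the windows. This lowers the weight of the event point. It does not reconcile the two anchors or the two primary time points, which this document states in conflict.

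The differing CCRe length is disclosed: "The guidelines allow for minor variations in the duration of the program (from 10 to12 weeks". Testing each arm at the end of its own programme is defensible, and a common test date has its own drawback, so neither is an error in itself.

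Two further inferences do not hold up. Visit timing might seem to reveal the arm to assessors, but the plan asks for the same assessor only where possible and blinds assessors to earlier results, so this is speculation. The reliability substudy, where "The retest is completed seven to 10 days after baseline assessment and prior to intervention start", shows that baseline can precede programme start by a week or more, but nothing ties it to one arm.

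**Conclusion.** The inconsistency is real and follows from the document's own figures. The baseline and completion definitions differ by two weeks for CCRe patients in six of eight hospitals, and the primary endpoint has two stated times. Under either anchor something differs by arm within those hospitals.

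The size depends on the reading. At the post visit, if it follows completion, CCRe has 20% more counting time in 12-week hospitals and about 15% across the arm, the latter assuming equal recruitment per hospital. At later visits the excess of 9.1%, 5.6% and 3.2% arises only under the completion anchor. Under the baseline anchor the difference is two weeks of time since completion. It would be too strong to conclude that the follow-ups cannot be compared: two weeks is about 3% of the period at week 62. The plan should be corrected because the ambiguity reaches the primary endpoint and the remedy is cheap.

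**What to change.** 1. Count admissions, hospital days, outpatient visits, exacerbations and deaths over the same fixed windows from randomization in both arms, for example 0–12, 0–22, 0–36 and 0–62 weeks, or analyse them as rates per person-time. With registry data this needs no extra visits.
2. Choose one anchor for the tests and questionnaires, including the primary 6MWD assessment. Say when CORe patients at 12-week hospitals are tested, and state it identically in the abstract, the Study design text and Table 1. Either anchor is a trade-off: a common date from baseline leaves time since completion unequal, and a completion date leaves time from baseline unequal. Name the one accepted.
3. Reword the purpose in the Background so that six months refers only to the register outcomes, in line with Table 1 and the section on changes to the initial plan.

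The cost is wording, plus a changed test date for some patients if the chosen anchor differs from current practice at a site. Neither programme needs to change.

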**Discussion:**

The study will likely contribute to knowledge regarding COPD tele-rehabilitation and to which extent it is more feasible and thereby more efficient than conventional COPD rehabilitation in patients with severe and very severe COPD.

**Trial registration:**

Clinicaltrials.gov Identifier: NCT02667171. Registration data: January 28th 2016.

## Background

Chronic Obstructive Pulmonary Disease (COPD) is a major cause of chronic morbidity and the fourth leading cause of death worldwide [1] (GOLD). COPD is characterized by increasing respiratory symptoms, frequent exacerbations and disability in activities of daily living. International and national guidelines emphasize that COPD rehabilitation is a key cornerstone in the standard treatment of COPD together with smoking cessation and pharmacological treatment [2–6]. The core elements of COPD rehabilitation is physical exercise training, patient-directed education and smoking cessation support, which are recommended as mandatory in standard COPD rehabilitation programs [2–6]. It is evident that COPD rehabilitation result in moderate to large clinically relevant improvements in quality of life, symptoms, anxiety and depression, walking distance, exercise tolerance and physical function in patients with mild as well as very severe stable COPD and in patients with acute phases of exacerbation [2–7]. However, approximately 50% of the patients with severe and very severe COPD decline to participate in COPD rehabilitation programs and 30–50% drop out before completion of the program [8–12]. The main reasons are severe symptoms and exacerbations, transportation distance and lack of energy [8–12]. There are no well-established rehabilitation alternatives for these patients, but supervised COPD tele-rehabilitation in groups delivered by health professionals in the patients’ own home via a computer, tablet or television screen could be a useful approach in terms of increasing compliance and adherence. Most studies on tele-rehabilitation in COPD have been non-randomized descriptive feasibility studies and they have reported promising effects on symptoms, physical function and quality of life [13–18]. Recently, results from three randomized controlled trials on tele-rehabilitation have been published [19–21]. In one study by Chaplin et al. (*n* = 103) [20] per protocol analyses showed equal results in regard to shuttle walk performance and COPD related symptoms when comparing effects of a short term (6–8 weeks) unsupervised web-based individually tailored home exercise program with a 7 week conventional pulmonary rehabilitation program comprising exercise and education. However, the dropout rate was higher in the web-based program (57% vs 23%). Another study by Vasilopoulou et al. (*n* = 150)^21^ showed that compared to a control group (usual care) the risk of acute COPD exacerbation and hospitalization was similar following a 12 months unsupervised individually tailored maintenance tele-rehabilitation exercise program combined with a weekly multidisciplinary telephone counseling and a 12 months supervised pulmonary maintenance rehabilitation program twice weekly at the hospital. However, compared to the other groups the tele-rehabilitation group had a reduced risk for visits to the emergency department. Finally, a small study by Tsai et al. (*n* = 37) [19] compared results from a non-exercising control group with results from a supervised 8-week tele-rehabilitation program in groups of 2–4 patients who could see and talk to both the physiotherapist and the other participants. The study showed significantly greater improvements in the endurance shuttle walk time (but not in the incremental shuttle walk time or the 6MWT), symptoms of anxiety and depression, and self-efficacy following the supervised tele-rehabilitation program.

Thus, the new results are promising, additional effects from face-to-face supervised COPD tele-rehabilitation in groups compared to outpatient supervised COPD rehabilitation in groups’ remains unanswered, i.e. potential higher compliance and effects when supervised and potentially better resource utilization when delivered in groups. To our knowledge this study protocol currently describes the first RCT study planned to investigate effects from equally face-to-face supervised and group based COPD rehabilitation in outpatient and tele-rehabilitation setting [22].

The purpose of our RCT study is to investigate the potential benefits of a 10-week supervised online COPD rehabilitation program (CORe) with conventional supervised COPD rehabilitation (CCRe) on walking distance (primary outcome), muscle endurance, physical activity level, quality of life, and COPD symptoms after completion of the intervention and at follow-up 3, 6 and 12 month later in patients with severe and very severe (stage III-IV) COPD. This paper describes the rationale and design of the study.

## Methods

### Study principles

The protocol follows the SPIRIT 2013 (Standard Protocol Items: Recommendations for interventional Trials) and the Template for Interventions Description and Replication (TIDieR) checklist for description of the interventions [23, 24]. Once completed the reporting will follow the CONSORT (Consolidated Standards of Reporting Trials) Statement for non-pharmacologic trials [25] (Fig. 1).

**Fig. 1 Fig1:**
[figure not shown]
Consolidate standards of reporting trials (CONSORT) flow diagram of trial design

### Study design

This study is a randomized controlled, assessor- and statistician blinded, superiority, multicentre trial with two parallel-groups. The trial investigates the effect of supervised COPD Online rehabilitation in groups, delivered by health professionals in the patients’ own home via a computer, in patients with severe and very severe (stage III-IV) COPD (ClinicalTrial.gov-identifier: NCT02667171). Patients from the University hospitals in the Capital Region of Denmark will be randomized to the supervised group-based online COPD rehabilitation (CORe) or to the conventional supervised COPD rehabilitation program (CCRe). The primary outcome will be the 6-min walking distance after completion of the COPD rehabilitation program (primary end point at 10/12 weeks). In addition, the study collects follow-up data at 3, 6 and 12 months after completion of the program which will be published in a separate paper (Fig. 1 and Table 1).

**Table 1 Tab1:** Study measures and outcomes to be collected

Variable	Baseline	10/12 weeks (post)	3-month follow-up (22-weeks)	6-month follow-up (36-weeks)	12-month follow-up (62-weeks)
Primary outcomes					
6 min walk distance (6MWD)	X	X	X		X
Secondary outcomes					
30s sit-to-stand test (30STS)	X	X	X		X
Clinical COPD Questionnaire (CCQ)	X	X	X		X
COPD Assessment Test (CAT)	X	X	X		X
Hospital Anxiety Depression Scale	X	X	X		X
EuroQol 5D (3-L)	X	X	X		X
Other variables and outcomes					
Attendance in rehabilitation		X			
Number of COPD related hospital admissions	X	X	X	X	X
Number of COPD hospital days	X	X	X	X	X
COPD related outpatient visits	X	X	X	X	X
Number of COPD exacerbations	X	X	X	X	X
Mortality	X	X	X	X	X
Exploratory outcome					
24 h–mobility (ActivePAL3tm; 5 days)	X	X	X		X
Descriptive variables					
Lung function	X				X
FVC	X				X
FEV1	X				X
FEV1/FVC%	X				X
FEV1% expected	X				X
Charlson morbity Index	X				X
Anthropometric measures					
Gender	X				
Age	X				
Weight	X	X	X		X
Height	X	X	X		X
Body Mass Index (BMI)	X	X	X		X
Self-reported measures					
Smoking status	X	X	X		X
Pharmacologic treatment	X	X	X		X

The primary hypothesis is that CORe is superior to CCRe due to a higher compliance and adherence to the CORe program. We expect a mean between-group difference of 26 m in the 6-min walk test after completion of the COPD rehabilitation programs (primary endpoint at 12-weeks).

We also expect clinically relevant improvements in both groups as a results of completing the COPD rehabilitation (Table 1).

